### Participants

#### Inclusion criteria

Diagnosis of a single tract perianal fistula not amenable to fistulotomy as determined by the supervising surgeonFistula must currently have a draining seton in placeAged >21 years oldWilling and able to provide informed consent for study participation and compliance with study protocolStated willingness to comply with all study procedures and availability for the duration of the study

#### Exclusion Criteria

Medical conditions that would, in the opinion of the investigator or treating provider, compromise the safety of the individual with study participation and/or the ability of the individual to follow study protocolGenito-urinary fistulization, including rectovaginal (i.e., fistulas that transverse the vaginal canal)Presence of an ileal anal pouchAny major surgery of the gastrointestinal tract (including one or more segments of the colon or terminal ileum) within 3 months prior to randomization; presence of stoma is not exclusionaryPrior surgical procedure (i.e., Ligation of Intersphincteric Fistula Tract or Endorectal Advancement Flap) for the target fistula or a perianal procedure that resulted in a large soft tissue defect within 6 months prior to screening visitOne or more of the following fistula types or anatomic presentations: horseshoe fistulas, fistulas that do not have an opening inside the anal canal or low rectum, blind ending sinus tracts (no external opening), branching fistulas (a previously performed conversion of a branching fistula tract to a single tract is not exclusionary), >1 internal opening, moderate or severe proctitis, severe rectal mucosal fibrosis surrounding the internal opening preventing the securing of the fistula plug disk, any anatomical limitation to successfully securing the fistula plug disk.Known allergic reactions to porcine collagen or yeast-derived productsCurrently enrolled in a drug or device trial or within 30 days of last investigational drug or device administration at baseline visit where investigational treatment (drug or device) was placed in or near the fistula tract or may potentially interact with study treatmentWomen who are known to be pregnant, breastfeeding, or planning to become pregnant, during the trialActive infection at the application siteThe presence of malignant neoplasms at the application sitePrior radiation therapy at the application site

#### Screen Failures

Screen failures are defined as participants who consent to participate in the clinical trial but are not subsequently randomized or the device is unable to be implanted. A minimal set of screen failure information is required to ensure transparent reporting of screen failure participants, to meet the Consolidated Standards of Reporting Trials (CONSORT) publishing requirements and to respond to queries from regulatory authorities. Minimal information includes demography, screen failure details, eligibility criteria, and any serious adverse event (SAE).

Individuals who consent and do not meet the criteria for participation in this trial (screen failure) because of the following criteria may be rescreened once the below criteria have been resolved.

No draining seton in placeActive infectionSurgical procedures outlined in the exclusion criteriaParticipation in an investigational study as outlined in exclusion criteriaPregnant or breastfeeding

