### Recruitment and Consent

This study aims to recruit 12 participants, that are adults >21 years of age regardless of gender, race, or ethnicity. There is no information currently available regarding differential agent effects in participants defined by race or ethnicity. No vulnerable populations are expected to be enrolled in this study. The target number of patients to be screened for enrollment is 60 with the expectation of enrolling and randomizing ~25% of those screened and accounting for discontinuation, withdrawal, and loss to follow-up. This will be a single-site study at VUMC with an anticipated accrual rate of 1–2 participants per month.

Existing patients, new patients, and provider-referred patients with a diagnosis of a complex perianal fistula that is not amenable to a fistulotomy can be recruited for this trial. Patients that are interested in the trial will be scheduled for a screening visit where they will sign written informed consent and undergo the baseline examination for eligibility. Informed consent is initiated prior to the individual’s agreeing to participate in the study and continues throughout the individual’s study participation. Informed Consent Forms (ICF) will be VUMC Institutional Review Board (IRB)-approved. Only those participants who undergo the baseline procedure will be considered treated and count towards total participant population. Participants who signed consent but did not receive treatment will not be followed further.

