### Outcomes

#### Primary outcome

The primary outcome of this study will be to evaluate the technical performance of rhPDGF-enhanced collagen implantation for treatment of complex perianal fistulas. This will be measured by the proportion of participants with procedural success as defined by implantation of the intervention without any intervention-related serious adverse events (SAEs) within 3 months of the procedure. The 3-month endpoint is the average timepoint when the surgeon makes the diagnosis that the perianal fistula has completely healed or failed to heal.

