#### Primary Outcomes Analysis

The primary endpoint is technical performance of the treatment. This will be reported as the proportion of participants assigned to the treatment arm with successful implementation of the treatment (without SAEs). This will be reported along with a Carlin-Louis 95% confidence interval.

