#### Secondary and Tertiary Outcomes Analysis

The secondary efficacy and safety endpoints will be analyzed for all randomized participants, as appropriate. Analyses will not be dependent on the findings of the primary endpoint. The first secondary endpoint considers all treatment-related adverse events and the proportion of participants with such events by arm will be analyzed/reported in the same way as the primary endpoint. The proportion will then be compared across arms using Fisher’s Exact test. If there are at least two participants with multiple treatment-related adverse events, a Mann-Whitney test will compare the number of adverse events per participant across arms.

The next secondary endpoint is fistula healing at Month 3 measured as a binary variable. The probability of healing in each arm will be calculated as the proportion of randomized participants per arm that are diagnosed as completely healed by a clinical evaluation of no visible drainage from the external opening at the Month 3 follow-up visit. The endpoint will be modeled as the outcome in a logistic regression model, conditioning on the treatment arm and baseline etiology. The effect will be presented as an adjusted odds ratio with a 95% confidence interval, as well as the marginal risk ratio after performing standardization. A p-value less than 0.05 will be considered statistically significant, but interpretation will be primarily focused on the 95% confidence interval. Residuals will be inspected to inspect model fit and validity of the homoscedasticity assumption. If model fit is poor, a Fisher’s Exact test will be used in place of logistic regression. Missing data are expected to be limited but will be handled using multiple imputation. Individuals who are lost to follow-up before Month 3 will also be included via the multiple imputation procedure, considering plausible imputations conditional on their baseline and Month 1 follow-up assessments, as well as weekly symptom data. The primary analysis will be modified intention-to-treat (ITT) based on randomized arm, as the investigational product is not available to patients who are not randomized to treatment before the Month 3 outcome assessment. It will be modified ITT in the sense that only participants who receive the investigational intervention will be analyzed as part of the intervention arm; this is necessary as some exclusion criteria cannot be assessed until the time of surgery.

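### The screen-failure rule contradicts the primary denominator: a failed implantation after randomization is a failure under one section and uncounted under another

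*Protocol article*

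**What the plan says.** Four sections of the protocol article bear on who is counted in the primary result.

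- **Primary outcome** defines "procedural success as defined by implantation of the intervention without any intervention-related serious adverse events (SAEs) within 3 months of the procedure". A participant can therefore fail in two ways: the implant is not placed, or a related SAE occurs.
- **Primary Outcomes Analysis** reports "the proportion of participants assigned to the treatment arm with successful implementation of the treatment (without SAEs". The Sample Size section also speaks of 8 participants assigned to the intervention arm.
- **Screen Failures** covers people who consent "but are not subsequently randomized or the device is unable to be implanted".
- **Recruitment and Consent** states: "Only those participants who undergo the baseline procedure will be considered treated and count towards total participant population". It adds: "Participants who signed consent but did not receive treatment will not be followed further".

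A fifth statement is related but sits elsewhere. In the Month 3 healing paragraph of the Secondary and Tertiary Outcomes Analysis, the modified ITT rule says that "only participants who receive the investigational intervention will be analyzed as part of the intervention arm". The reason given is that "this is necessary as some exclusion criteria cannot be assessed until the time of surgery".

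**The concern.** Placing the implant is the first component of the primary endpoint, so a participant in whom it cannot be placed is exactly what the endpoint exists to record. The screen-failure definition puts that participant outside the trial. Its two limbs are alternatives: the first already covers people who were not randomized, so the second adds something only if it reaches people who were.

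At stake is the meaning of the headline result. The Sample Size section reads 8 successes out of 8 as strong evidence against a low probability of successful implementation. That inference needs failures to be countable. In an arm of 8, classifying one person differently changes the reported proportion visibly.

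**Working it through.** **Reproducing the plan's figure.** When all n participants succeed, the two-sided 95% Clopper-Pearson lower bound is 0.025^(1/n). For n = 8 this is 0.025^(1/8) = 0.6306, which agrees with the 0.63 in the Sample Size section. The arithmetic is right; its interpretation depends on the denominator.

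**The sections side by side, for a participant randomized to the intervention whose implant cannot be placed**

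| Section | Treatment of this participant |
|---|---|
| Primary outcome, Primary Outcomes Analysis, Sample Size | In the denominator, counted as a failure |
| Screen Failures | Screen failure |
| Recruitment and Consent | Not followed further if regarded as untreated; in or out of the counted population depending on whether an abandoned attempt is a baseline procedure |
| Modified ITT sentence (Month 3 healing) | Not analysed in the intervention arm |

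No section says which of these prevails.

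**Size.** The protocol gives no implantation-failure rate, so the failure counts below are hypothetical. Related SAEs are set to zero. The bounds are Clopper-Pearson 95%, as in the planning calculation. For x < n, the lower bound is the 0.025 quantile of Beta(x, n − x + 1).

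| Scenario | Failures removed (lower bound) | Failures counted (lower bound) |
|---|---|---|
| 8 assigned, 1 failed, not replaced | 7/7 = 100% (0.59) | 7/8 = 87.5% (0.47) |
| 8 assigned, 2 failed, not replaced | 6/6 = 100% (0.54) | 6/8 = 75% (0.35) |
| 1 failed, replaced until 8 are implanted | 8/8 = 100% (0.63) | 8/9 = 89% (0.52) |
| 2 failed, replaced until 8 are implanted | 8/8 = 100% (0.63) | 8/10 = 80% (0.44) |

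The protocol does not say outright whether such participants are replaced, so both cases are shown.

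**What 8/8 would mean.** If failures are counted, the chance of 8 implantations in 8 attempts is p^8, where p is the true implantation probability: 0.66 at p = 0.95, 0.43 at 0.90, 0.17 at 0.80 and 0.06 at 0.70. An 8/8 result then carries information about p. If failures are removed, the implantation component is 100% at every p and carries none.

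**Interval method.** The Primary Outcomes Analysis will report a Carlin-Louis interval, not Clopper-Pearson. Under an assumed Beta(1,1) prior, which the protocol does not state, the lower bound is 0.66 for 8/8, 0.55 for 8/9 and 0.52 for 7/8. The levels shift, but the gap between removing and counting remains.

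**The case against.** The strongest reply is that the one section specifying the primary analysis uses the right denominator. It speaks of those assigned, as does the Sample Size section, and on those terms a failed implantation counts against the implant. This stands. A reader might infer that every implantation failure is deleted, or that the endpoint cannot record one. The documents do not support that. They show a contradiction, and the endpoint can in any case still fail through a related SAE.

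Three further points also stand.

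- The modified ITT sentence closes the Month 3 healing paragraph, and its reference to a primary analysis most naturally means the main analysis of that secondary endpoint. It should not be read as clearly governing the primary endpoint.
- Under Administration, the procedure begins with examination under anesthesia, seton removal and curettage. Someone in whom implantation was attempted and failed has arguably undergone the baseline procedure and so would count under Recruitment and Consent.
- Some exclusions can be judged only at surgery. They include anatomy that prevents the plug disk from being secured, so non-implantation may sometimes reflect ineligibility and not technical failure. The order of randomization and this examination within the baseline visit is not stated.

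The Screen Failures section also keeps minimal details and any SAE for CONSORT reporting. Such cases would appear in the participant flow, but that does not put them in the primary proportion.

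None of this reconciles the sections. The screen-failure wording still covers a randomized participant whose implant cannot be placed, and it does not separate ineligibility found at surgery from a failed attempt.

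**Conclusion.** Wrong as written. The protocol contradicts itself on the primary denominator, and one of the competing rules removes the failures that the endpoint is meant to measure. If the screen-failure rule is followed, only a related SAE can lower the result.

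One failed implantation among 8 assigned then moves the estimate from 87.5% to 100% and the Clopper-Pearson lower bound from 0.47 to 0.59. These figures rest on a hypothetical failure count, no related SAE and the planning interval. A reader might also infer that the 0.63 bound is met however many implantations fail. That holds only if failures are replaced until 8 are implanted and no related SAE occurs; without replacement the bound falls to 0.59 or 0.54.

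**What to change.** 1. In Screen Failures, limit the term to participants who are not randomized.
2. In Primary Outcomes Analysis, define the denominator as all participants randomized to the intervention arm, and count every attempted but failed implantation as a procedural failure with its reason listed.
3. Report separately, with reasons, participants found at the examination under anesthesia, before any implantation attempt, to meet a pre-specified exclusion criterion. Add a sensitivity analysis that counts them as failures. Counting non-implantation for any reason in the main analysis would charge such ineligibility to the implant's technical performance. The sensitivity analysis matters because the operating investigator, who is unblinded, is the one at the table when the distinction is made.
4. Align Recruitment and Consent and the modified ITT sentence with these rules, and say whether an abandoned attempt counts as undergoing the baseline procedure.

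As an alternative to step 3, randomize after that eligibility check. Enrolment has begun, so this could apply only to participants not yet randomized.

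The cost is wording in the protocol and any analysis plan, plus one sensitivity analysis. The reported success proportion may be slightly less favourable.

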### Randomization and Blinding

Randomization will occur at the baseline visit at a ratio of 2:1 intervention versus control. Randomization will be stratified to achieve balance in treatment allocation across idiopathic and CD-related fistula types. Because the total sample size is 12, randomization will be blocked using blocks of size 3 (2:1 intervention to control) within each stratum (idiopathic versus CD-related). Based on historical clinical data we anticipate enrolling 9 Chron’s participants and 3 idiopathic participants. Blinding of the patients, surgeons other than the investigator performing the procedure, and study team members assessing outcomes to study arm allocation will be employed to reduce bias in conducting study activities and evaluations. Given that the control group will be receiving a routine care procedure, the investigator who will be performing all procedures will be unblinded to the treatment assignment for each participant. To maintain blinding while assessing outcomes, clinical exams during follow-up study visits will be performed by another surgeon not involved in the initial screening visit or the procedural encounter. In the case of a serious adverse event or medical emergency in which knowledge of the treatment is necessary for the participant’s well-being or medical care, the unblinded investigator will be alerted to ensure appropriate medical management.

### Intervention

rhPDGF is highly purified, aseptically processed, and sterile filled into transparent glass syringes. One syringe contains a 0.5 mL solution of 0.3 mg/mL rhPDGF in 20 mM sodium acetate buffer pH6+/−0.5. rhPDGF is stored at 2°C to 8°C and then allowed to reach room temperature prior to administration to the patient. Up to 4 mL of the rhPDGF (0.15–1.2 mg) solution will be used to rehydrate a collagen matrix manufactured from porcine collagen sourced from veterinary pigs. The native collagen molecules and fiber structures are maintained, and no additional materials are added. Antigens, lipids, and non-collagenous proteins are removed through extraction and purification steps rendering the material acellular and reducing the likelihood of acute and chronic biological reactions. The collagen membranes are available in three different sizes: 20×30 mm (model 500662), 30×40 mm (model 500663), and 40×50 mm (model 500664) and can be trimmed as needed. All components of the intervention are biocompatible and absorbable and will only be implanted once.

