### Administration

The following procedures will be performed by the surgeon for administration of the intervention.

A clinical examination under anesthesia with an anal fistula probe will be conducted to rule out active infection, anal stenosis, or active proctitis and confirm the presence of a single fistula tract.The seton will be removed, the fistula tract curetted vigorously to remove granulation tissue lining the tract, and the tract will be flushed with saline.The fistula tract length and diameter and amount of the sphincter muscle involved will be assessed by the surgeon with an anal fistula probe placed from the external to the internal opening.The appropriate model collagen matrix will be used based on the length of the tract.The collagen will be saturated with the rhPDGF solution in a sterile dish for a minimum of 10 min.After the collagen is fully saturated with rhPDGF, it will be pulled through the fistula tract carefully from the internal opening to the external opening.The collagen will be sutured to the rectal mucosa at the internal opening and any portion beyond the skin level will be trimmed to sit flush with the external opening.

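### The article gives two conflicting answers for an intervention tract the largest membrane cannot span: drop the participant, or count a primary-outcome failure

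*Protocol article*

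**What the plan says.** **Implant.** Intervention lists three sheets: "The collagen membranes are available in three different sizes: 20×30 mm (model 500662), 30×40 mm (model 500663), and 40×50 mm (model 500664"). The sheets may be trimmed. Administration then states: "The appropriate model collagen matrix will be used based on the length of the tract". The sheet is drawn from the internal to the external opening, sutured inside and cut level with the skin.

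**Eligibility.** Inclusion criteria and Exclusion Criteria contain no limit on tract length. The nearest item excludes "any anatomical limitation to successfully securing the fistula plug disk", which concerns fixation.

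**Order of events.** At screening, patients "undergo the baseline examination for eligibility". Randomization and Blinding says: "Randomization will occur at the baseline visit at a ratio of 2:1 intervention versus control". Administration begins with a probe examination under anesthesia. It continues "The seton will be removed, the fistula tract curetted vigorously to remove granulation tissue lining the tract", and only then "The fistula tract length and diameter and amount of the sphincter muscle involved will be assessed by the surgeon with an anal fistula probe".

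**Non-implantable cases.** Screen Failures includes consented participants in whom the device cannot be placed. Secondary and Tertiary Outcomes Analysis restricts the intervention arm to those who actually receive the intervention, because some exclusions can be checked only at surgery.

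**Primary outcome.** Primary outcome defines procedural success as implantation without an intervention-related serious adverse event within 3 months. Primary Outcomes Analysis reports it as a proportion of participants assigned to the treatment arm.

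**The concern.** The administration steps presuppose a sheet at least as long as the tract, and the article gives no rule for a tract that no listed sheet can span. Such a case would come to light at surgery. How it is then classified matters, because implantation is itself the primary outcome. If the participant is called a screen failure or a non-recipient, the event that the endpoint is meant to detect disappears from it. If the participant stays in the denominator, the same event is a failure.

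The loss would also be largely one-sided. Under Efficacy Assessments, Crohn's disease controls have seton removal and debridement with no implant, so none can be lost for implant fit. A selective loss after randomization would then affect the comparison of healing as well as the primary proportion.

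**Working it through.** **1. Geometry.** The largest listed sheet has a long edge of 50 mm. Trimming is allowed, so the longest straight run is its diagonal: √(40² + 50²) = √4100 = 64 mm. Some length is used by the internal suture and the trim at the skin. No tract length appears in the article to compare with these figures.

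**2. Timing.** Randomization and Blinding says only that allocation takes place at the baseline visit. The modified intention-to-treat rule is justified by exclusions that can be checked only at surgery. That justification is needed only if allocation comes before the surgical check. The order is therefore a strong inference, not a statement.

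**3. The planned figure.** Sample Size gives a Clopper-Pearson 95% lower bound of 0.63 for 8 of 8. For n successes out of n the two-sided bound is 0.025^(1/n). With n = 8 this is 0.025^(1/8) = 0.631, so the plan's figure is reproduced.

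**4. One or two non-implantable tracts among the 8.** For x < n the lower bound is the 2.5% quantile of Beta(x, n − x + 1).

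| Handling | One case | Two cases |
|---|---|---|
| Counted as failure among those assigned | 7/8: 0.47 | 6/8: 0.35 |
| Removed, not replaced | 7/7: 0.59 | 6/6: 0.54 |

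For one case the point estimate is 7/8 = 87.5% or 7/7 = 100%, a gap of 12.5 percentage points. Recruitment and Consent counts only those who undergo the baseline procedure towards the total, so replacement cannot be ruled out. The result could then read 8/8 with a bound of 0.63, and the failure would not show.

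**5. Choice of interval.** Primary Outcomes Analysis names a Carlin-Louis interval in place of Clopper-Pearson. Assuming a uniform prior, the lower bounds are 0.66 for 8/8 (0.025^(1/9)), 0.63 for 7/7 (0.025^(1/8)) and 0.52 for 7/8 (2.5% quantile of Beta(8, 2)). The gap between the two ways of handling the case remains.

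**6. How often.** The documents do not allow this to be computed. If q is an assumed share of eligible tracts that cannot be spanned, the chance of at least one among 8 is 1 − (1 − q)^8:

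| q (assumed) | Chance of at least one |
|---|---|
| 0% | 0% |
| 5% | 34% |
| 10% | 57% |
| 20% | 83% |
| 30% | 94% |

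**7. One-sidedness.** The article expects 9 Crohn's disease and 3 idiopathic participants. With 2:1 allocation in blocks of 3, that gives 9/3 = 3 Crohn's disease controls and 3/3 = 1 idiopathic control. Three of the four expected controls would therefore have no implant.

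**The case against.** The strongest reply is that the premise is not shown. A reader might infer that long tracts are being randomized to an implant that cannot reach, but no eligible tract is shown to exceed 50 mm, and the true share may be zero. That objection stands.

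Two further inferences also go beyond the text:

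- **That the tract is first measured after randomization and seton removal.** The intraoperative measurement is the only one described. Screening includes an eligibility examination, and a probe examination precedes seton removal. The assessment sections describe the screening examination as visual inspection of the external opening, but that does not prove that length is never gauged earlier.
- **That only one membrane may be used.** No such limit is stated. The sheets can be trimmed ("40×50 mm (model 500664) and can be trimmed as needed"), and more than one is not ruled out.

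The full protocol, which is not shown here, may hold a length criterion or sizing instructions. The missing length limit is therefore not in itself a fault of the article. The dimensions of the commercial plug are not given, so nothing can be said about fit in idiopathic controls. Seton removal also occurs in both control procedures, so it is not peculiar to the intervention.

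It is also fair that the article anticipates non-implantable cases through its screen-failure definition, the modified intention-to-treat rule and the surgeon's discretion to exclude. But these provisions create the conflict with a primary outcome that counts implantation among those assigned. The modified rule sits in the paragraph on Month 3 healing, so its reach over the primary endpoint is unclear. The screen-failure definition has no such restriction. Finally, the conflict would arise for any failed implantation. Membrane length is one foreseeable route to it, and one that could be checked before allocation.

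**Conclusion.** The point holds in a limited form. The article prints no tract-length limit, lists no sheet larger than 40×50 mm, and describes length measurement only during surgery, apparently after allocation. If an intervention participant's tract cannot be spanned, the sections on screen failures and modified intention-to-treat conflict with those on the primary outcome and its denominator. One such case moves the lower bound from the planned 0.63 to 0.59 or 0.47, depending on which section is followed. Crohn's disease controls cannot be lost this way.

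This rests on 8 intervention participants, on no replacement for the 0.59 figure, and on the inference that allocation precedes the surgical check. The frequency is unknown and may be zero. The documents do not support saying that the trial does randomize tracts its implant cannot span.

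**What to change.** Reconcile Inclusion criteria, Exclusion Criteria, Screen Failures, Intervention, Administration, Primary outcome and the analysis sections so that one rule covers a participant in whom the implant cannot be placed. Specifically:

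- At the probe examination under anesthesia already planned, confirm for every participant that the tract can take an available membrane, and open the allocation only afterwards. A patient who does not pass is then a screen failure before randomization, and the check applies equally to both arms.
- After allocation, count any failure to implant as a primary-outcome failure in the assigned arm, and keep that participant in the denominator.

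No length limit or operative rule is proposed; those are for the investigators. The cost is small. The allocation must be opened in the procedure room, and a few patients may be excluded before randomization. The investigator performing the procedures is already unblinded, and follow-up examinations are done by another surgeon, so blinded outcome assessment need not change.
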